### Plans to promote participant retention and complete follow-up {18b}

Study participants are reminded to complete questionnaires by email and push notifications. Subsequently, patients are contacted by telephone and reminded to complete questionnaires.

Deviations from the study protocol are noted in the study database.

Study participants whose data sets are no longer usable in the context of the study due to deviations from the study protocol are assigned to a third group, the comparison group, and are also surveyed after 1 year.

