### Trial design {8}

PRO-P is a multicenter, prospective, and two-arm 1:1 randomized controlled study.

Randomization, stratified by study center (6 centers) and age (< / ≥ 70), is performed 6 weeks after surgery and directly linked to the first post-surgery survey. Patients with symptoms of urinary incontinence (≥ 1 pad/day, 6 weeks after surgery) will be randomized. Patients with no symptoms of urinary incontinence (0 pads/day 6 weeks after surgery) will be assigned to the comparison group (see Fig. 1).

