**Fig. 1 Fig1:**
[figure not shown]
SPIRIT figure. Pre-op. = pre-operative; post-op. = post-operative; QoL = quality of life. *Comparison group: patients who are 6 weeks postoperatively urinary continent; **Survey of patients in the intervention group only

Patients in the intervention group will be offered medical support, if defined thresholds of symptom burden are exceeded (e.g. at least one minimally important difference (MID) for EPIC domains). ePROMs in the control group will not trigger proactive study intervention and patients will receive standard-of-care management according to local guidelines. ePROM measures in the control group will serve as a reference for the trial population.

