### Outcomes {12}

#### Summative evaluation

##### Primary outcome

To calculate the primary endpoint, the difference is calculated between the scores on the urinary incontinence scale of the EPIC-26 [38] at 52 and 6 weeks postoperatively. Changes regarding urinary incontinence (minimally important difference (MID) ≥ 9) at 52 weeks postoperatively compared with 6 weeks postoperatively are considered. The primary endpoint will be examined in an intention-to-treat analysis. The comparison regarding superiority of the primary endpoint will be performed by using a mixed linear model for repeated measures. The variables included in the model comprise intervention/control group, time, group*time, center, tumor stage, and age group.

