### Sample size {14}

Based on the information that preoperative urinary continence issues are observed in 3% [35] and a continence rate of 20% (0 pad/day) is anticipated 6 weeks postoperatively [7], the required sample size is calculated as follows: A total of 672 patients who undergo prostatectomy at participating centers will be considered for inclusion in the study. Of these, 412 are expected to be excluded for the following reasons: 336 patients (50%) will not provide informed consent, 10 patients (3%) will have preoperative urinary incontinence, and 66 patients (20%) will show no urinary incontinence 6 weeks postoperatively. The remaining 260 patients will be randomized, with 130 assigned to the intervention group and 130 to the control group. Data analysis will be conducted for 104 patients in each group, with 26 patients (20%) anticipated to be excluded from analysis due to dropout (see Fig. 4).

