### Data management {19}

Disease- and treatment-related data will align with the “OncoBox Prostate” data structure in all German Cancer Society-certified prostate cancer centers.

Primary data collection: All primary cases are created by the participating clinics for the statutory cancer registration in the tumor documentation system (TuDok). The clinics then check whether the patient fulfills the inclusion criteria during a face-to-face contact with a study physician. If not, this is indicated in TuDok. If the inclusion criteria are met, the patient is informed about the study and asked for consent; the result is noted in the TuDok. A prerequisite for inclusion is that the patient has a digital device. If consent is given, the patient is included in the study and created in the ePROM application. The data is stored together with the patient's e-mail address in encrypted form in the TÜV-certified Telekom Health Care Cloud. The declaration of consent with name and address remains at the center. Study participants fill out questionnaires in the ePROM application. As soon as questionnaires are assigned, notifications are sent to the study participants via the ePROM application (push messages via an app and e-mail reminders). Questionnaires are transferred pseudonymized by means of a study ID from the survey software via an interface to the web-based study documentation Pro-P-Doc. As all clinical information (diagnosis and therapy) is already documented in the tumor documentation system at this point, this data can be transferred to the study documentation via the OncoBox Prostata (a current list of fields can be found in the OncoBox specification: http://www.xml-oncobox.de/de/Zentren/ProstataZentren) and merged with the pre- and post-therapeutic survey data. The study center also documents relevant study information such as (a) whether the patient continues to meet the inclusion criteria, (b) whether the patient was randomized to the intervention or control group, (c) whether and if so, which form of intervention was offered to the patient, and (d) whether the patient took advantage of it. The survey data can also be transferred from Pro-P-Doc to the hospital information system together with selected master and clinical data in the form of a pseudonymized (study ID) PDF; this is done manually by the study nurses at the center, who keep the pseudonymization keys so that a clear assignment to the electronic patient file is possible.

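### The rule moving protocol deviators to the comparison group is not limited to unrandomised men, so as written it contradicts the intention-to-treat analysis

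*Protocol article*

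**What the plan says.** Four statements in the protocol article bear on this point.

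- **Retention {18b}.** The rule covers "Study participants whose data sets are no longer usable in the context of the study". If the cause is a protocol deviation, they "due to deviations from the study protocol are assigned to a third group, the comparison group, and are also surveyed after 1 year". Deviations in general are only recorded in the study database.
- **Outcomes {12} and Statistical methods {20a}.** Both sections state: "The primary endpoint will be examined in an intention-to-treat analysis". The model is a mixed linear model for repeated measures with a group-by-time term.
- **Trial design {8}.** "Patients with symptoms of urinary incontinence (≥ 1 pad/day, 6 weeks after surgery) will be randomized". By contrast, "Patients with no symptoms of urinary incontinence (0 pads/day 6 weeks after surgery) will be assigned to the comparison group". The legend of Fig. 1 repeats the definition: "Comparison group: patients who are 6 weeks postoperatively urinary continent".
- **Sample size {14}.** "Data analysis will be conducted for 104 patients in each group, with 26 patients (20%) anticipated to be excluded from analysis due to dropout".

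The section on non-adherence and missing data {20c} offers multiple imputation as a sensitivity analysis. It has no rule for reassigned men. The blinding section {17a} states that participants, care providers and data analysts are all unblinded.

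**The concern.** Under intention-to-treat, a deviation does not make a randomised patient's data unusable and does not change the arm in which he is counted. A rule that moves him to another group because of something that happened after randomisation does the opposite. If the men moved differ in outcome from those who stay, and the two arms lose different numbers or kinds of men, the comparison is no longer the randomised one.

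Two features make this more than loose wording. The trigger is not defined, so someone must judge case by case whether a data set is still usable. The trial is open label with unblinded analysts, so that judgement could be made with the allocation known.

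The receiving group is affected too. It is meant to hold men who were continent at week 6, whereas randomised men had at least 1 pad/day by definition. Adding deviators would mix the two.

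**Working it through.** **1. Setting the passages side by side**

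| Question | What the article gives |
|---|---|
| Who may be moved? | Study participants with unusable data; no restriction to men before randomisation {18b} |
| What makes data unusable? | Protocol deviations, with no criterion given {18b} |
| Where do they go? | The comparison group {18b}, defined as 0 pads/day at week 6 {8, Fig. 1} |
| Who is analysed for the primary endpoint? | Intention-to-treat {12, 20a} |
| Are moved men still analysed in their arm? | Not stated anywhere, including {20c} |

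For a randomised man, the first and fourth rows cannot both hold unless the last row were answered yes.

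**2. The plan's own sample size**

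Inputs from Sample size {14}: d = 0.4, 80% power, 5% two-sided, 130 randomised per group, 20% dropout.

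- n per group = 2 × (1.960 + 0.842)² / 0.4² = 2 × 7.851 / 0.16 = 98.1, rounded up to 99. This matches the article; the t-test solution is 99.08.
- 130 × 0.8 = 104 per group, also as stated. Power with 104 is 82.2%; with all 130 it would be 89.7%.

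The arithmetic is sound. The issue is the analysis population.

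**3. Illustration of bias**

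The documents give no deviation rate, outcome gap or imbalance between arms, so all of these are assumptions. A share f of the intervention arm only is moved, those men do g SD worse than those kept, and the true effect is zero.

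- Bias = f × g (in SD units)
- SE = √[1/(n(1 − f)) + 1/n]
- Type I error = P(|Z + bias/SE| > 1.96)

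Worked case with n = 104, f = 0.20, g = 0.5: bias = 0.10; SE = √(1/83.2 + 1/104) = 0.147; bias/SE = 0.68; type I error = 10.4%.

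| f | g | Bias (SD) | Share of d = 0.4 | Type I error, n = 104 | Type I error, n = 130 |
|---|---|---|---|---|---|
| 10% | 0.5 | 0.05 | 12.5% | 6.4% | 6.8% |
| 20% | 0.5 | 0.10 | 25% | 10.4% | 11.8% |
| 20% | 1.0 | 0.20 | 50% | 27.5% | 33% |

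The two n columns take 104 or 130 per arm before anyone is moved. If the moved men did better than those kept, the bias would have the opposite sign.

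**4. The benign case**

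If removal is equal in both arms and unrelated to outcome, there is no bias and only power is lost. From 82.2% with 104 per group, power falls to 80.3% (5% removed), 78.1% (10%) or 73.2% (20%).

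**The case against.** The strongest reply is that the retention section never says the men concerned are randomised. Patients consent before surgery {26a} and are randomised 6 weeks after it, linked to the first postoperative survey {8}. A man who misses that survey could not be randomised, and following him in a third group would leave intention-to-treat untouched. The rule may also have been meant only for survey scheduling. Both readings are possible, so the text does not establish that randomised men have been or will be removed. But the article states neither limit. Speaking of a third group presupposes the two randomised arms, and data that are no longer usable were presumably usable once. Even on the pre-randomisation reading, men not shown to be continent would enter a group defined by continence.

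A reader might infer more than the documents support:

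- **That every deviator is moved.** Only those whose data are judged unusable are.
- **That the intervention arm has more scope to deviate because it has more contacts.** No section treats a missed survey, an unanswered call or a declined consultation as a deviation that makes data unusable. The intervention description {11a} provides for men who decline consultation or cannot be reached.
- **That the sample-size section sets an exclusion rule.** Going from 130 to 104 is an attrition allowance, loosely worded. The stated mixed model can use the earlier surveys of men without a week-52 value.
- **That the data-management field recording "whether the patient continues to meet the inclusion criteria" leads to removal.** It is a documentation item {19}, and nothing links it to the analysis set.

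**Conclusion.** The point holds as a conflict between stated rules. As written, the reassignment rule can take randomised men out of their arm on an undefined criterion. That contradicts the intention-to-treat statement, and no other section keeps those men in place. It also conflicts with the definition of the comparison group. This is not detail left to an analysis plan, because an analysis plan could not follow both rules if the first reaches randomised men.

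The documents do not show that a breach of intention-to-treat has occurred, nor that the primary p-value is invalid. The size and direction of any bias cannot be derived from them. The figure of 0.05–0.10 SD with a type I error of about 6–12% rests wholly on an assumed one-sided scenario: 10–20% of the intervention arm alone moved, with outcomes 0.5 SD worse. With balanced removal unrelated to outcome, the bias is zero.

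**What to change.** 1. State that every randomised patient is analysed in his allocated arm whatever his deviations or adherence, using all his available EPIC-26 data.
2. Limit the reassignment rule to men never randomised, and define when a data set counts as no longer usable.
3. Report reassigned men who were not continent at week 6 separately from the continent comparison group.
4. Make sure the 1-year survey of any randomised man affected by the rule includes the EPIC-26 incontinence scale. The retention section does not say what that survey contains.
5. Put any deviation-based exclusion in a per-protocol analysis labelled as supportive.
6. As a minor wording change, let Sample size {14} say that 104 per group are expected to have week-52 data, rather than that 26 are left out of the analysis.

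The cost is protocol and analysis-plan wording, plus restoring any randomised man already moved to his allocated arm in the analysis data set. The sample size does not change. A 1-year survey of these men is already planned, so extra data collection is needed only if it lacks the incontinence scale.

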### Data management {19}

Disease- and treatment-related data will align with the “OncoBox Prostate” data structure in all German Cancer Society-certified prostate cancer centers.

Primary data collection: All primary cases are created by the participating clinics for the statutory cancer registration in the tumor documentation system (TuDok). The clinics then check whether the patient fulfills the inclusion criteria during a face-to-face contact with a study physician. If not, this is indicated in TuDok. If the inclusion criteria are met, the patient is informed about the study and asked for consent; the result is noted in the TuDok. A prerequisite for inclusion is that the patient has a digital device. If consent is given, the patient is included in the study and created in the ePROM application. The data is stored together with the patient's e-mail address in encrypted form in the TÜV-certified Telekom Health Care Cloud. The declaration of consent with name and address remains at the center. Study participants fill out questionnaires in the ePROM application. As soon as questionnaires are assigned, notifications are sent to the study participants via the ePROM application (push messages via an app and e-mail reminders). Questionnaires are transferred pseudonymized by means of a study ID from the survey software via an interface to the web-based study documentation Pro-P-Doc. As all clinical information (diagnosis and therapy) is already documented in the tumor documentation system at this point, this data can be transferred to the study documentation via the OncoBox Prostata (a current list of fields can be found in the OncoBox specification: http://www.xml-oncobox.de/de/Zentren/ProstataZentren) and merged with the pre- and post-therapeutic survey data. The study center also documents relevant study information such as (a) whether the patient continues to meet the inclusion criteria, (b) whether the patient was randomized to the intervention or control group, (c) whether and if so, which form of intervention was offered to the patient, and (d) whether the patient took advantage of it. The survey data can also be transferred from Pro-P-Doc to the hospital information system together with selected master and clinical data in the form of a pseudonymized (study ID) PDF; this is done manually by the study nurses at the center, who keep the pseudonymization keys so that a clear assignment to the electronic patient file is possible.

The Pro-P-Doc web application is provided on a server. The complete data set is retrieved from Pro-P-Doc at regular intervals. When patients are created in Pro-P-Doc, a consecutive ID (Pro-P-Doc ID) is assigned. In this step, the data is only pseudonymized using the PRO-P-Doc ID (removal of the study and OncoBox ID, deletion of personal data, age at first diagnosis instead of date of birth, Pro-P-Doc ID) and transferred to OncoBox Research Pro-P.

For qualitative research, contact forms containing patients’ real names, contact details, and study IDs are stored in a trust center on protected IMVR servers so that patients can be contacted directly for interviews. Interviews are pseudonymized by a trust center (study ID) and transcribed by external service providers. The audio recordings are then destroyed. All text passages that could be used to identify third parties are removed from the transcripts, so that the transcripts are pseudonymized in relation to the patients and anonymized in relation to third parties. In order to merge the interview data with the survey data (PDF from Pro-P Doc), the survey data can be requested from the study nurse of the center concerned, stating the study ID. The respective survey data set (PDF from Pro-P Doc) is then transmitted to the IMVR pseudonymized (study ID).

### Confidentiality {27}

Patient data is processed pseudonymized; see the “Data management” section.

### Plans for collection, laboratory evaluation, and storage of biological specimens for genetic or molecular analysis in this trial/future use {33}

N/a.

No biological specimens will be collected.

## Statistical methods

### Statistical methods for primary and secondary outcomes {20a}

#### Summative evaluation

##### Primary outcome

To calculate the primary endpoint, the difference is calculated between the scores on the urinary incontinence scale of the EPIC-26 at 52 and 6 weeks postoperatively. Changes regarding urinary incontinence (minimally important difference (MID) ≥ 9) at 52 weeks postoperatively compared with 6 weeks postoperatively are considered. The primary endpoint will be examined in an intention-to-treat analysis. The comparison regarding the superiority of the primary endpoint will be performed by using a mixed linear model for repeated measures. The variables included in the model comprise intervention/control group, time, group*time, center, tumor stage, and age group.

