## Interventions

### Explanation for the choice of comparators {6b}

In the control group, ePROMs will be collected 6, 24, and 52 weeks after radical prostatectomy, but without further measures. Therefore, they will receive treatment according to the current clinical routine [2].

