**Fig. 2 Fig2:**
[figure not shown]
Schematic representation of the intervention

In the intervention group, ePROMs (EPIC-26, PHQ-4) are obtained after 6, 12, 18, 24, 36, and 52 weeks. If cut-off values are exceeded, an alert is triggered at the prostate cancer treatment center (PCC). In order to ensure that ePROMs are filled in within a defined time-frame, ePROM statuses will be closely monitored by the study nurses. In addition to electronic reminders, patients will be reminded by study nurses via phone calls in a structured manner.➔ An alert is dealt with by a study nurse who makes a standardized telephone contact with the patient.➔ Asking about symptoms and offering to coordinate consultation with a trained urologist at the PCC. Content of the consultation: a medical history, clinical examination, and detailed consultation, as well as, if necessary, the guideline-compliant initiation of further diagnostics and therapy, including follow-up contacts necessary in this context.➔ Before consultation, urologists receive a written summary and visualization of the ePROM test results in the clinic information system.

In addition, postal communication of a report on the results of a urological consultation at the PCC or, if the patient has either not indicated a need for consultation in the telephone contact with the study nurse or has not been reached by the study nurse, of the ePROM results to the outpatient urologist.

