### Participant timeline {13}

EPROMs will be issued in a standardized fashion once before and six times (intervention group) or three times (control group) after radical prostatectomy in patients with localized PC (see Fig. 3).

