**Fig. 4 Fig4:**
[figure not shown]
Consort data flow

To detect a mean effect size of 0.4 (Cohen’s *d*) for the primary endpoint, 99 patients per group are required, assuming 80% power and a 5% two-sided error.

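### The primary model compares week-6-to-week-52 change without adjusting for the week-6 score, which gives up precision by an amount the documents do not fix

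*Protocol article*

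**What the plan says.** In the Primary outcome text, which appears under Outcomes {12} and again under Statistical methods {20a}, the endpoint is formed as follows: "the difference is calculated between the scores on the urinary incontinence scale of the EPIC-26 at 52 and 6 weeks postoperatively". The comparison is to be "performed by using a mixed linear model for repeated measures", and the terms are listed: "The variables included in the model comprise intervention/control group, time, group*time, center, tumor stage, and age group". Neither place names the week-6 score as a covariate or states that the arms share a common week-6 mean.

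The week-6 score is a baseline in the strict sense. Under Trial design {8}, randomisation "is performed 6 weeks after surgery and directly linked to the first post-surgery survey". Both arms supply the score. For controls, section {6b} says: "In the control group, ePROMs will be collected 6, 24, and 52 weeks after radical prostatectomy". For the intervention arm, the text with Fig. 2 says: "In the intervention group, ePROMs (EPIC-26, PHQ-4) are obtained after 6, 12, 18, 24, 36, and 52 weeks". Randomisation is stratified by center and age group only.

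The section on missing data {20c} applies the same type of model to the secondary outcomes.

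**The concern.** The value of the outcome at randomisation is often the strongest available predictor of its later value. Subtracting it is not the same as adjusting for it. Subtraction fixes the regression slope of week 52 on week 6 at 1, whatever the data show. If the true slope is lower, the change score carries week-6 noise into the comparison, and a chance difference between arms at week 6 pulls the estimated effect the other way through regression to the mean.

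The plan already adjusts for center, tumor stage and age group, so covariate adjustment is accepted in principle. What is at stake is power and protection against chance imbalance, and both can be had from data the trial already collects. The margin is not wide: 104 analysed per arm against 99 required, out of 130 randomised. Dropout of about 24% (1 − 99/130 = 23.8%) instead of the planned 20% would use it up.

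**Working it through.** **Inputs from the protocol article.** Effect size: "To detect a mean effect size of 0.4" (Cohen's d) on the primary endpoint, taken here as 0.4 SD of the change score; two-sided 5%; 80% power; 99 per group required; 130 per group randomised; 20% dropout, leaving 104.

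**Assumed, because the documents do not give them.** ρ, the correlation between the week-6 and week-52 scores, from 0.3 to 0.7; k = SD6/SD52, from 0.6 to 1.2.

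**1. The plan's own figure.** n per group = 2(1.960 + 0.842)²/0.4² = 98.1, rounded up to 99. This reproduces. Also 130 × 0.8 = 104. Power at 104 per arm = Φ(0.4 × √(104/2) − 1.960) = Φ(0.924) = 82.2%.

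**2. What the listed terms estimate.** If the response is the difference, week 6 is plainly not adjusted for. If week 6 is instead one of the repeated responses, the listed group main effect leaves the week-6 means free to differ, and the group-by-time contrast at week 52 is again the difference in change. A generalised least squares check with complete data at weeks 6, 24 and 52, unit SDs and 99 per group confirms this:

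| ρ | Free week-6 means | Change score | Common week-6 mean, or week-6 covariate |
|---|---|---|---|
| 0.3 | 0.0283 | 0.0283 | 0.0184 |
| 0.5 | 0.0202 | 0.0202 | 0.0152 |
| 0.7 | 0.0121 | 0.0121 | 0.0103 |

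(Entries are variances of the week-52 contrast.)

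**3. The general comparison.** Per patient:

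- Var(change) = SD6² + SD52² − 2ρ·SD6·SD52
- Var(adjusted) = SD52²(1 − ρ²)
- Difference = (SD6 − ρ·SD52)², which is never negative and is zero only when ρ = k

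The variance ratio, adjusted to change, is (1 − ρ²)/(1 + k² − 2ρk). With equal SDs (k = 1) it reduces to (1 + ρ)/2.

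**4. Size of the gain.** Variance reduction, with power at 104 per arm in brackets (change score alone: 82.2%), holding the effect at 0.4 SD of the change:

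| k | ρ = 0.3 | ρ = 0.5 | ρ = 0.7 |
|---|---|---|---|
| 0.6 | 9% (86%) | 1% (83%) | 2% (83%) |
| 0.8 | 22% (90%) | 11% (86%) | 2% (83%) |
| 1.0 | 35% (95%) | 25% (91%) | 15% (88%) |
| 1.2 | 47% (98%) | 40% (96%) | 33% (94%) |

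At k = 0.6 and ρ = 0.6 the gain is nil. With k = 1, the number per group that gives 80% power falls from 99 to 64, 74 and 84.

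**5. Chance imbalance.** At 104 per arm the standard error of the week-6 mean difference is √(2/104) = 0.139 SD. An absolute difference of 0.2 SD or more arises by chance with probability about 15% (z = 0.2/0.139 = 1.44). With k = 1 and ρ = 0.5 the slope is 0.5, so a 0.2 SD imbalance shifts the change contrast by 0.2 × (1 − 0.5) = 0.1 SD. The SD of the change is then √(2 × 0.5) = 1 SD, so the shift is a quarter of the targeted 0.4.

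**The case against.** The strongest reply is that nothing here is wrong. Under 1:1 randomisation a change-score comparison is unbiased and holds its type I error. The sample size was set on the stated endpoint and reproduces, and power is about 82% as planned. All of this stands. A reader might infer from the missing covariate that the primary result would be biased or the trial underpowered; the documents support neither.

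The second reply is about size. A reader might take the equal-SD gain of 15–35% as assured. It is not. Only men using at least one pad a day at week 6 are randomised, which may narrow the spread at week 6, while week-52 scores can run from persistent incontinence to recovery. If so, k is below 1 and the gain may be small or nil. This also stands, although k below 1 is itself an assumption. Part of the week-6 variation may already be explained by center, tumor stage and age group, so ρ and k should be read as values after adjustment for those terms.

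The third reply is that the article is a condensation and an unseen analysis plan may include the baseline score. That is possible. But the article does not leave the covariates open: it gives the same list twice, and the week-6 score is on neither. If the analysis plan already adjusts, the published list needs correcting.

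**Conclusion.** The point holds as an efficiency loss. On either reading of the model, with complete data, the listed terms yield an unadjusted change-score contrast at week 52, although the randomisation-time score is available in both arms. Adjustment cannot have larger variance in large samples, and it estimates the same treatment effect. Its benefit, for assumed correlations of 0.3 to 0.7 and SD ratios of 0.6 to 1.2, runs from nil to a 47% reduction in variance; the documents do not allow a narrower statement. The change is worth making because it needs no new data and removes the exposure to chance week-6 imbalance, not because the present plan is invalid.

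**What to change.** Keep the endpoint and the week-52 contrast as stated. For the post-randomisation visits, add the week-6 urinary incontinence score and its interaction with time as covariates. Week 6 then serves as a covariate and not also as a response. Alternatively, keep week 6 as a response and constrain its mean to be equal across arms. Treat secondary scales the same way where a week-6 value exists. How the intervention arm's extra visits at weeks 12, 18 and 36 enter the model is a separate choice that this change does not settle.

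The cost is a small documented amendment. The model is stated in the protocol, so both the protocol and the analysis plan should be changed, and section {25} sends relevant protocol changes to the ethics committees. The amendment should be dated before outcome data are examined, because section {17a} says the analysts are not blinded and a later addition could look data-driven. No patients, data or procedures are added, and the sample size can stay as it is.
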